**Appendix L**

**Lay Counselor Record**

Patient Name ______________________________ CTC Number ____________

Age ____________ Sex ____________

| **Date of Visit**  **(dd/mm/yyyy)** | **Visit Length (minutes)** | **Topics Discussed** | **Next Steps / Patient Goal** | **Counselor’s Name** | **Comments**  (If partner tested note details here–when, where, etc.) | **Date of Next Appointment**  **(dd/mm/yyyy)** |
| --- | --- | --- | --- | --- | --- | --- |
|  |  | **Discussed:**  ⁮ HIV status disclosure to partner(s)  ⁮ partner(s) HIV testing  ⁮ safer sex  ⁮ alcohol use  ⁮ preparing for ART  ⁮ ART adherence  ⁮ **Tested partner for HIV** |  |  |  |  |
|  |  | **Discussed:**  ⁮ HIV status disclosure to partner(s)  ⁮ partner(s) HIV testing  ⁮ safer sex  ⁮ alcohol use  ⁮ preparing for ART  ⁮ ART adherence  ⁮ **Tested partner for HIV** |  |  |  |  |
|  |  | **Discussed:**  ⁮ HIV status disclosure to partner(s)  ⁮ partner(s) HIV testing  ⁮ safer sex  ⁮ alcohol use  ⁮ preparing for ART  ⁮ ART adherence  ⁮ **Tested partner for HIV** |  |  |  |  |

**Appendix M**

**Health Care Provider Observation Form**

Instructions: To be completed while observing a health care provider during a clinic appointment with a patient.

Observer ID #: __________

Health Care Provider ID #: __________

Date of interview: ( _____ **/** _____ **/** __________)

dd mm yyyy

Assessment Number:

_____ 1. Baseline assessment

_____ 2. 6-month assessment

_____ 3. 12-month assessment

Patient session start time**:** __________

Patient session end time**:** __________

Total visit time**:** __________ minutes *[Calculate after visit is over]*

1. Is the HIV prevention poster on the wall in the office?

_____ 0. No

_____ 1. Yes

2. Is the HIV prevention one-page job aid in a place where it can be easily viewed and/or used?

_____ 0. No

_____ 1. Yes

3. What was patient’s primary reason for clinic visit?

_____ 1. Routine scheduled visit

_____ 2. Acute illness. Describe what patient presented to provider**:**

_______________________________________________________________

_______________________________________________________________

_______________________________________________________________

4. If patient had acute illness or something else that did not allow provider to conduct HIV prevention activities, tick box below and do not complete remainder of questionnaire.

_____ 1. HIV prevention not conducted due to acute patient illness.

_____ 2. HIV prevention not conducted due to other reasons.

Specify why: _______________________________________________________________

_______________________________________________________________

_______________________________________________________________

For each of the items below, circle whether the provider discussed the topic with the patient. If provider did not discuss the topic, provide information about why the provider did not discuss.

|  | **No** | **Yes** | ***Not applicable*** |
| --- | --- | --- | --- |
| 5. Assess whether the patient is sexually active | 0 | 1 | *-3* |
| 6. *(if yes)* Discuss partner(s) HIV status | 0 | 1 | *-3* |
| 7. *(if sexually active)* Ask whether partner has (or partners have) been tested for HIV | 0 | 1 | *-3* |
| 8. Assess whether patient has disclosed to sex partner(s) | 0 | 1 | *-3* |
| 9. *(if has not disclosed to partners)* Encourage disclosure to sex partner(s) | 0 | 1 | *-3* |
| 10. Discuss adopting safer sex behaviors | 0 | 1 | *-3* |
| 11.Discuss abstaining from sex | 0 | 1 | *-3* |
| 12. Discuss reducing number of sex partners | 0 | 1 | *-3* |
| 13. Discuss being faithful to one partner | 0 | 1 | *-3* |
| 14. Discuss using condoms *every time* patient has sex | 0 | 1 | *-3* |
| 15. Explain negative consequences of sex without a condom | 0 | 1 | *-3* |
| 16. Assess alcohol use | 0 | 1 | *-3* |
| 17. *(if needed)* Advise on risky alcohol use and refer to counselor | 0 | 1 | *-3* |
| 18. Assess adherence to ARVs | 0 | 1 | *-3* |
| 19. Assess adherence to other medications | 0 | 1 | *-3* |
| 20. *(if needed)* Refer for adherence counseling | 0 | 1 | *-3* |
| 21. Assess for signs/symptoms of STIs by asking STI screening questions | 0 | 1 | *-3* |
| 22. *(if STI symptoms present)* Conduct exam for STIs | 0 | 1 | *-3* |
| 23. *(if STI symptoms present)* Prescribe treatment | 0 | 1 | *-3* |
| 24. *(if STI symptoms present)* Give Contact Slip for partner STI management | 0 | 1 | *-3* |
| 25. Assess patient/partner pregnancy status | 0 | 1 | *-3* |
| 26. Assess patient/partner pregnancy intentions | 0 | 1 | *-3* |
| 27. Offer appropriate family planning counseling and services | 0 | 1 | *-3* |
| 28. *Tick one of the following:*  ⁮ 1. if pregnant, counsel then refer to PMTCT  ⁮ 2. if does not desire pregnancy, discuss and provide contraception if desired by patient  ⁮ 3. if desires pregnancy, then discuss safer conception methods |  |  |  |
| 29. Encourage patient to work on an HIV prevention goal | 0 | 1 | *-3* |
| 30. Give patient HIV prevention handouts | 0 | 1 | *-3* |
| 31. Give patient condoms  If condoms given, how many? ____________ | 0 | 1 | *-3* |
| 32. Refer patient to lay counselor | 0 | 1 | *-3* |
| 33. Refer patient to other services or clinic. Specify: ____________ | 0 | 1 | *-3* |

| 34. Write reasons why health care provider did not discuss HIV prevention activities. |
| --- |

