***Provider and Counselor Observation Checklists***

Assessing the effectiveness of the intervention package on behavioral, biologic, and service delivery outcomes depends on whether, and how accurately, health care providers and lay counselors deliver the intervention. In order to determine how the intervention changes service delivery, project staff will observe providers and lay counselors in the intervention clinics during approximately 3% of routine patient visits over the one year project period. Health care providers and counselors (where available) in comparison clinics will also be observed to have a complete assessment of standard of care visits and services provided in these the comparison clinics. At the beginning of each month, days will be randomly selected for observing health care providers and lay counselors. The number of observations per week will depend on the number of patients being seen at each clinic per week. For each observation, the observers will sit in as unobtrusive a place as possible in the room with the health care provider or lay counselor and will note which intervention activities are discussed with participants by health care providers (Appendix M) and lay counselors (Appendix N). Comparisons will then be made between the care provided at intervention clinics and the standard of care being delivered in comparison clinics.

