**Limitations of study**

Potential problems may arise, given that this is a large, multi-site project in a resource-limited setting; thus, alternate plans will be developed. Because attrition may be high, approximately 30% when following HIV-positive patients across one year, baseline sample size will be large to ensure statistical power to detect subtle behavior changes. Also, clinics are extremely busy with high patient volume, and providers may find incorporating the intervention into their routine clinic visits difficult. If all providers do not administer the intervention to all patients (i.e., some patients do not receive the intervention), measuring the effectiveness of the intervention will be difficult. Thus, fidelity measures (e.g., observation, questionnaires) are included in the project to ensure providers and lay counselors conduct the intervention as designed. In addition, the questionnaire data are all self-report, which is potentially subject to socially desirable responding, recall biases, or forgetting.

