| 23. Write reasons why lay counselor did not discuss HIV prevention activities. |
| --- |

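### Item 4 of the provider observation form leaves the topic checklist blank at visits coded as prevention not conducted, and its open-ended second code overlaps with an ordinary No

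*Protocol*

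**What the plan says.** Appendix M is filled in by project staff who watch a provider's visit. Table 2 schedules the observation checklists at baseline, 6 months and 12 months. The section on health care provider and lay counselor assessment sets observation at about 3% of visits in both arms.

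Item 4 tells the observer what to do if the patient had an acute illness or "something else that did not allow provider to conduct HIV prevention activities, tick box below and do not complete remainder of questionnaire". Two codes are offered: "HIV prevention not conducted due to acute patient illness" and "HIV prevention not conducted due to other reasons". The second has space to specify why.

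The checklist begins straight after item 4, with topics scored No, Yes or Not applicable and this instruction: "If provider did not discuss the topic, provide information about why the provider did not discuss". Item 34, at the end of the form, reads "Write reasons why health care provider did not discuss HIV prevention activities".

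The lay counselor form (Appendix N) has no stop. It runs through its checklist and ends with "Write reasons why lay counselor did not discuss HIV prevention activities".

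On use, the section on observation checklists says comparison clinics are observed so that usual-care visits and services are fully described. It continues: "Comparisons will then be made between the care provided at intervention clinics and the standard of care being delivered in comparison clinics". The limitations section gives the problem to guard against, in the clause beginning "If all providers do not administer the intervention to all patients", and names observation among the fidelity measures that answer it.

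**The concern.** The observations are the protocol's only direct view of what happens in the consulting room. The other sources are reports by patients, providers and counselors, and abstracted records. A form meant to show how far the package is delivered should be most informative at visits where delivery failed, and at those visits this form goes blank on content.

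Two consequences follow. First, an observed visit can contain services that belong on the checklist even though counseling was displaced. A patient who presents acutely with genital symptoms may be examined and treated, and may be given condoms or a referral. Items 21 to 24 and 31 to 33 would record this, but item 4 permits leaving them empty.

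Second, the other-reasons code has no boundary. The protocol repeatedly expects shortage of consultation time. One observer could treat that as something that did not allow prevention and stop; another could score each topic No and explain at item 34.

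At stake is the description of fidelity and of the service contrast between arms, which will be needed to interpret the trial result, particularly a null one.

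**Working it through.** No figure in the protocol depends on this point, so there is nothing to reproduce. The check has two parts.

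**Routing of visits through the form**

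| Visit | Path on Appendix M | What is recorded |
|---|---|---|
| Some or all topics delivered | Items 5 to 34 | Topic scores, with reasons for those not covered |
| Nothing delivered, nothing prevented it | Items 5 to 34 | No on each applicable topic, reasons at item 34 |
| Acute illness prevented it | Stop at item 4, code 1 | Identifiers, date, times, poster and job-aid status, reason for visit, tick |
| Something else prevented it | Stop at item 4, code 2 | As above, plus a written reason |

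Rows 2 and 4 differ only in whether the observer judges that something prevented delivery, and the form gives no criterion. The same visit can therefore yield 29 scored items (5 to 33) or 29 blanks.

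**Arithmetic of the denominator**

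Inputs, all assumed because the protocol gives none:
- p is the delivery rate of a topic among completed forms: 0.80 in intervention clinics and 0.30 in comparison clinics.
- s is the share of observed visits stopped at item 4, varied from 0 to 50%.

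If stopped visits delivered nothing, the all-visit rate is p × (1 - s). The completed-form rate is p, so it is too high by the factor 1/(1 - s):
- s = 10%: 1/0.90 = 1.11
- s = 30%: 1/0.70 = 1.43
- s = 50%: 1/0.50 = 2.0

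The completed-form difference between arms is always 0.80 - 0.30 = 0.50. The all-visit difference depends on s in each arm:

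| s, intervention | s, comparison | All-visit rates | All-visit difference |
|---|---|---|---|
| 0% | 0% | 0.80, 0.30 | 0.50 |
| 10% | 10% | 0.72, 0.27 | 0.45 |
| 30% | 30% | 0.56, 0.21 | 0.35 |
| 50% | 50% | 0.40, 0.15 | 0.25 |
| 30% | 10% | 0.56, 0.27 | 0.29 |
| 50% | 10% | 0.40, 0.27 | 0.13 |
| 10% | 30% | 0.72, 0.21 | 0.51 |
| 10% | 50% | 0.72, 0.15 | 0.57 |

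Completed forms overstate the contrast in most rows and understate it in the last two.

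For services that may have been given at a stopped visit, scoring blanks as zero is not safe either. If such a service was given at an unknown rate q in stopped visits, the true rate is p × (1 - s) + q × s. With p = 0.80 and s = 30%, it lies anywhere from 0.56 (q = 0) to 0.56 + 0.30 = 0.86 (q = 1). The blanks do not say where.

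**The case against.** The strongest reply is that nothing disappears. A stopped form carries an explicit statement that prevention was not conducted, so an analyst can keep the visit in the denominator as non-delivery. On the prevention topics the bias is then zero. No section says these visits are excluded, and the denominator is a choice that an analysis plan may make. This stands, and it rules out the tempting reading that zero-delivery visits drop out of the fidelity data.

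The trigger is also narrower than any visit without prevention. It requires that something did not allow delivery. A provider who could have delivered but did not is scored No throughout and does reach item 34. A reader might infer that item 34 is seen only when prevention was at least partly done; the form does not support that.

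A third argument is that adherence, STI care, pregnancy intentions and condoms are themselves among the protocol's five prevention steps. If the tick is right, zero is right for them too. This has force only if every observer takes prevention in that wide sense. The form does not say so, and an observer could tick acute illness because counseling was displaced while an examination or treatment took place. The point reduces the problem without removing it.

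The expected effect of time pressure is partial delivery spread over visits, which is scored normally. Patient report by topic, provider questionnaires, chart review and clinic service counts give further evidence on delivery. Appendix N covers dedicated counseling sessions, so its lack of a stop is a difference in design and not a contradiction.

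**Conclusion.** The concern holds as a minor weakness of the form. Item 4 discards item-level content at visits where something prevented prevention work, and it leaves code 2 undefined against an ordinary No. Later analysis can restore the denominator, but it cannot recover services that were never recorded or undo inconsistent coding between observers.

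The size is unknown because the protocol gives no stop frequency. Overstatement by 1/(1 - s) rests on two assumptions: only completed checklists are analysed, and stopped visits delivered nothing.

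A reader might go further and infer that comparison clinics lose visits most often, so that the contrast shrinks. For example, with stops at 30% and 70% and delivery of 0.80 and 0.60 on completed forms, the all-visit rates are 0.80 × 0.70 = 0.56 and 0.60 × 0.30 = 0.18. The difference is then 0.38 against 0.20 on the forms. Those rates are assumed, and nothing in the protocol supports them. Usual care that simply does not offer prevention is not something that prevented it, and other assumed rates reverse the direction.

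The primary outcome is patient self-report and is not touched.

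**What to change.** In Appendix M item 4, delete the closing clause that tells the observer to leave the rest of the form blank. Have items 5 to 34 completed at every observed visit in both arms, and keep item 4 with its two codes as a recorded reason. Report fidelity and the between-arm comparison over all observed visits, with a second figure that excludes acute-illness visits only.

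The cost is slightly more form completion by an observer who is already in the room; no extra staff or visits are needed.

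If the skip is kept, the lesser remedy is to define code 2 against an ordinary No and to state that stopped visits count as non-delivery. That settles the denominator but leaves the service content unrecorded.

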**Hypotheses**

Project hypotheses focus on the effectiveness of the prevention intervention package on behavioral outcomes, biologic outcomes, and delivery of services in the HIV care and treatment settings. Intervention clinics will integrate the HIV prevention intervention package into routine care of HIV-positive patients; comparison clinics will provide standard of care to HIV-positive patients.

Compared to participants attending comparison HIV clinics, participants at intervention clinics will be more likely over a 12-month period to report or show a(n):

Behavioral

- Decrease in unprotected vaginal and anal sex
- Decrease in number of sex partners
- Increase in number of sex partner(s) getting an HIV test
- Increase in disclosure of HIV status to sex partner(s)
- Decrease in alcohol use
- Increase in adherence to HIV antiretroviral medications

Biologic

- Decrease in unintended pregnancy or partner pregnancy
- Decrease in STIs (i.e., urethral discharge)

Service Delivery

Compared to the comparison clinics, the intervention clinics will:

- Provide more family planning counseling (e.g., safer pregnancy) and services (e.g., contraception) to HIV-positive women and their partners

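### Appendix M, items 27 and 28, cannot record contraception discussed apart from contraception provided, so the observed comparison between arms cannot isolate provision

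*Protocol*

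**What the plan says.** Appendix M lists provider activities as items 5 to 33. Every row has No, Yes and Not applicable codes except item 28, whose cells are blank. Item 28 instead carries the instruction "Tick one of the following" and three boxes:

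- Box 1: "if pregnant, counsel then refer to PMTCT"
- Box 2: "if does not desire pregnancy, discuss and provide contraception if desired by patient"
- Box 3: "if desires pregnancy, then discuss safer conception methods"

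The row above it, item 27, is coded No, Yes or Not applicable and reads "Offer appropriate family planning counseling and services". Items 25 and 26 use the same codes for whether pregnancy status and pregnancy intentions were assessed. Item 33 codes referral to other services, with space to specify. Item 34 is free text for reasons why prevention activities were not discussed.

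The Provider and Counselor Observation Checklists section gives the purpose: "In order to determine how the intervention changes service delivery, project staff will observe providers and lay counselors in the intervention clinics". It extends observation to the comparison clinics and plans a comparison of care between the two groups of clinics. The service delivery hypothesis is that intervention clinics will "Provide more family planning counseling (e.g., safer pregnancy) and services (e.g., contraception) to HIV-positive women and their partners". The list under Primary Outcome Variables also names family planning counselling and family planning services as separate entries.

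**The concern.** Item 28 has three faults of construction.

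1. It mixes patient status with provider action. A tick in box 2 could mean that the patient does not want a pregnancy, that contraception was discussed, or that a method was given.
2. Two boxes hold two actions each. Box 2 joins discussing and providing contraception. Box 1 joins counselling and referral to PMTCT.
3. It has no code for none of these actions, and it is not made conditional on items 25 to 27. If the provider raised nothing, the observer must tick on status alone or leave the item blank.

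The second fault matters most. Dispensing pills or injections inside the HIV clinic is a central part of the family planning component, and the hypothesis names counselling and services separately. Observation is the one visit-level measure that depends neither on what the provider charted nor on what the patient recalls. It ought therefore to show whether intervention clinics gave methods or only talked about them. Once a visit has ended, the form cannot supply the missing distinction.

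**Working it through.** No sample size, power or error-rate figure enters this point, so there is no figure in the plan to reproduce. The check is which events can be told apart from items 25 to 28 read together.

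**Combinations of items 27 and 28**

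| Item 27 | Item 28 | What can be read |
|---|---|---|
| No | blank, or any box | Family planning was not offered; a tick can only describe status |
| Yes | box 3 | Safer conception was discussed |
| Yes | box 2 | Contraception discussed only, or discussed and provided: one code for both |
| Yes | box 1 | Counselling and PMTCT referral: one code for both |
| Yes | blank | Something was offered, but not which service |

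**What this does to the provision comparison**

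Let s be the proportion of observed visits in an arm with item 27 Yes and box 2 ticked, and p the proportion at which a contraceptive method was given. Assume a method is given only at visits with that combination. The form then fixes only

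0 ≤ p ≤ s.

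With subscripts I for intervention and C for comparison, the difference satisfies

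−s_C ≤ p_I − p_C ≤ s_I.

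- If s_I and s_C are both above zero, the interval includes negative and positive values, so the sign of the provision difference is not determined.
- If s_C is zero, p_C is zero and the difference lies between 0 and s_I. The sign cannot then be negative, but the size remains unknown.
- A larger number of observed visits estimates s more precisely. It does not narrow the bounds themselves.

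**What can still be read**

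The arm difference in any family planning offered comes directly from item 27. Whether status and intentions were asked comes from items 25 and 26.

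**Comparison with the rest of the form**

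STI care is split into screening, examination, treatment and contact slip (items 21 to 24), each with its own code. Condoms given have their own row and a count (item 31). The family planning actions are not separated in this way.

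**The case against.** The strongest reply is that the form and the other instruments already cover most of this, and much of that reply stands.

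- A reader might infer that no observed family planning difference can be read. The form does not support that: item 27 codes offered or not offered at each visit.
- A reader might also infer that usual care would look like the package, because the observer must tick a box in item 28 even when nothing was delivered. Such a visit would score No on item 27, and No on items 25 and 26 if the questions were not asked. A tick in item 28 does not override those codes.
- A reader might infer that the service delivery hypothesis is left without usable data. It is not. The Clinic Services Form (Appendix O) counts pills and injections separately each month. Chart review (Appendix P) records, by appointment, PMTCT referral, methods, who supplied them and whether safer pregnancy was discussed. The Patient Questionnaire (Appendix H) asks about family planning topics raised by the provider (Q4c, Q4e, Q4f), who last supplied a woman's method (P8f), and referral to a family planning clinic (Q9b).
- Observation covers about 3% of visits, by patients who need not be enrolled. The Study design and locations and Limitations of study sections treat it as a fidelity measure.
- Item 33 can hold a PMTCT referral, which softens the complaint about box 1, although the form does not direct the observer to record it there.

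The reply does not reach the merging of discussion with provision. Item 27 has the same defect, and the other sources measure something different: clinic-level monthly totals, charted entries with no row for contraception discussed, and patient recall over six months. Observer training could settle how a tick is read, but it could not add codes that the form lacks.

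**Conclusion.** The point holds in a limited form. Items 27 and 28 do not let the observer record contraception discussed and contraception provided as separate events. Box 1 merges counselling with PMTCT referral in the same way. Item 28 also confuses status with action and has no code for none done.

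The consequence falls only on the observation comparison described under Provider and Counselor Observation Checklists. There, the arm difference in contraception actually provided is bounded by −s_C and s_I and cannot be separated from discussion. No numerical size can be given, because the protocol states no expected rates of discussion or provision. The bounds assume that methods are given only at visits coded Yes on item 27 with box 2 ticked.

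The primary outcome, its power and the other measures of family planning services are unaffected. This is a minor, inexpensive improvement to a data collection form.

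**What to change.** Replace item 28 with:

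1. One patient-status line: pregnant / does not desire pregnancy / desires pregnancy / not established.
2. Separate rows, each coded No, Yes or Not applicable:
   - contraception discussed
   - contraceptive method provided at this visit
   - safer conception discussed
   - PMTCT counselling given
   - PMTCT referral made

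Keep item 27 as the overall indicator, items 25 and 26 for whether status and intentions were asked, and item 33 for other referrals. Give observers one rule for when Not applicable is used, the same in both arms, so that denominators match. Compare the arms on the action rows.

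The cost is one status line and five short rows in place of one item, with a matching change to the data entry screen. No visits, staff or participants are added. The change concerns only what the observer records, not what care is given.
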